### Assessments

Both patients and relatives will be assessed multiple times during the study period. Briefly, assessments are scheduled at (1) baseline, where sociodemographic data of both patients and relatives as well information on illness history and psychopharmacological treatment will be obtained, (2) within 2 weeks after the relatives have attend the fourth and last group session, and (3) at 9-month follow-up. A flow diagram for assessments during the study period is shown in Table 1.

**Table 1 Tab1:**
[figure not shown]
Flow diagram for enrollment, interventions and data collection at baseline and follow-up

*FAD* The Family Assessment Device (36-items), *FAS* The Family Attitude Scale, *FMSS* The Five Minute Speech Sample, *HAM-D*
_*6*_ Hamilton six-item subscale, *MINI* MINI International Neuropsychiatric Interview, *PC* Perceived Criticism Scale, *SAPAS* The Standardized Assessment of Personality-Abbreviated Scale, *SCL-90-R* The Symptom Checklist-90-Revised, *SDS* The Sheehan Disability Scale, *WHO-5* The World Health Organization Well Being Index

Furthermore, telephone calls will be made to patients every 6 weeks in the follow-up period in order to obtain information on the presence of depressive symptoms measured by the HAM-D_6_.

Patients will be told to contact the principal investigator when recognizing a worsening of depressive symptoms. Furthermore, the patients’ medical records will be screened in order to identify information on relapse. Both the relatives and private psychiatrists have the opportunity to contact the principal investigator if they suspect a depressive relapse.

### Measures

The diagnosis of major depressive disorder is verified by use of the MINI. The MINI will also be applied in order to screen for the presence of axis-I comorbid psychiatric disorders according to the *Diagnostic and Statistical Manual of Mental Disorders, 4th Edition* (DSM-IV). The MINI is a short, structured diagnostic interview, with an administration time of approximately 15 min, that assesses the most important axis-I diagnoses, according to the DSM-IV and the ICD-10 [25].

Furthermore, patients are screened for DSM-IV axis-II disorders using The Standardized Assessment of Personality-Abbreviated Scale (SAPAS), a structured interview consisting of eight items [37] which has been shown to have adequate clinical applicability in patients with a primary diagnosis of depression [38].

Patient-reported outcomes include the following measures: the Major Depression Inventory (MDI) is a questionnaire containing 10 depressive symptoms from both the ICD-10 and the DSM-IV, with a specific timeframe of the previous 2 weeks. Each item is scored from 0 to 5, and the 10 items are summed to a total score. The MDI can be used as either a rating scale for assessment of the degree of depressive symptoms *or* as a diagnostic tool [39] with cutoff scores for mild, moderate and severe depression, respectively [40]. The Hamilton six-item subscale (HAM-D_6_) is a self-rating scale covering the core symptoms of the HAM-D_17_ [41]. The HAM-D6 has high clinical validity [42] as well as adequate psychometric validity [43]. The World Health Organization Well Being Index (WHO-5) consists of five questions and is one of the most used questionnaires in the measurement of subjective psychological wellbeing [44]. The Sheehan Disability Scale (SDS) is a three-item self-report measure of disability and impairment within the domains of work, social life and family life [45]. The Perceived Criticism Scale (PC) is four-item scale used to assess how critical the patients consider themselves to be of their relative and how critical the patients consider the relative to be of them [10].

Assessment instruments filled out by the relatives include the WHO-5 as well as the following:

The Symptom Checklist-90-Revised (SCL-90-R) consists of 90 items and assesses symptoms of psychopathology within nine different symptom dimensions [46].

Expressed emotion (EE) is measured by The Family Attitude Scale (FAS) [47] and The Five Minute Speech Sample (FMSS) [36]. The FAS is a measure of EE rated by the relatives themselves. It consists of 30 items and assesses self-reported critical and hostile attitudes towards the patient.

In the FMSS the relative is instructed by an interviewer to talk about their thoughts and feelings regarding the patient. The relative is told to speak for 5 min without the interviewer asking questions or otherwise interrupting. The speech sample is recorded and later coded by a trained rater in order to classify the relative as either “High EE” or “Low EE.”

The FMSS is an alternative to the very time consuming “gold standard” way to measure EE, the Camberwell Family Interview (CFI) [48]. FMSS has been found to be a feasible method to evaluate EE in families of patients with mood disorders [49]; predictive validity with regard to the clinical outcome of depression has also been demonstrated [50].

Furthermore, a modified version of The Family Assessment Device (FAD) [51] will be used. The modified version consists of 36 items and two subscales measuring wellbeing and illbeing aspects of family functioning, respectively [52]. This new version of the FAD will, furthermore, be psychometrically validated as a part of the current study.

In order to quantify the relatives’ experience with participation in the groups, they will after the last group session fill out a modified version of the WHO treatment satisfaction questionnaire [53].

### Outcomes

#### Primary outcome

The primary outcome is occurrence of depressive relapse defined as a score ≥7 on the HAM-D_6_ [54] in the 9-month follow-up period (hypothesis 1) among remitted patients.

#### Secondary outcomes

Secondary outcomes are time to relapse, defined as the number of weeks from baseline to relapse; time to full remission defined as a HAM-D_6_ score <5 [54] among the partially remitted patients (hypothesis 2); and the reduction of depressive symptoms in the HAM-D_6_-score (hypothesis 3).

A number of exploratory questions will be examined in regard to the impact of the two interventions: for patients’ depressive symptoms (MDI), subjective wellbeing (WHO-5), disability (SDS), family functioning (FAD) and perceived criticism (PC), and for the relatives: subjective wellbeing (WHO-5), family functioning (FAD) and EE (FAS and FMSS).

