**Method/design:**

The study is designed as a dual center, two-armed, observer-blinded, randomized controlled trial. Relatives are randomized to participate in one of two conditions: either four sessions of manualized family psychoeducation or four sessions in a social support group led by a health care professional. Patients will not participate in the groups and will continue their treatment as usual. A total of 100 patients, each accompanied by one relative, will be recruited primarily from two outpatient clinics in the Capital Region of Denmark.

The primary outcome is the occurrence of depressive relapse at 9-month follow-up defined as a score ≥7 on the Hamilton six-item subscale. Secondary outcomes will include time to relapse.

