### Aim

The aim of the present study is to compare an intervention consisting of FPE to an active control intervention of social support for relatives of patients with a diagnosis of major depression.

The following hypotheses are proposed:Psychoeducational intervention for relatives will reduce the risk of depressive relapse (defined as a score on The Hamilton six-item subscale, HAM-D_6_ ≥ 7), among remitted depressed patients (HAM-D_6_ < 7) compared to the active control conditionPsychoeducational intervention for relatives will reduce the time to achieve full symptomatic remission (defined as HAM-D_6_ < 5) among partially remitted depressed patients (HAM-D_6_ = 8–12) compared to the active control conditionPsychoeducational intervention for relatives will reduce depressive symptoms (measured on the HAM-D_6_) among currently depressed patients (HAM-D_6_ ≥ 13), compared to the active control condition

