## Method

### Design

The study is a dual center, two-armed, observer-blinded, randomized controlled trial investigating the effect of FPE compared to an active control group on the course of the illness in patients with a diagnosis of major depression.

The study is divided into two phases, an intervention phase and a follow-up phase. During the first phase the relatives will, after inclusion and baseline assessments, be randomised to one of two conditions comprised of four weekly sessions, of either a FPE program (intervention group) or social support for relatives (active control group).

The second phase is a follow-up conducted 9 months after completion of treatment involving the assessment of both patients and relatives.

The 9-month follow-up period was selected as a previous study has found a significant effect of FPE, reducing the risk of relapse within that timeframe [19]. Furthermore, this timeframe allowed for the collection, analysis and reporting of results within the course of a 3-year PhD project.

All patients during the study period will continue their TAU at the outpatient clinic or with their private psychiatrist. Treatment decisions will not be affected by the patients’ decision to participate or not in the study and there will be no restrictions regarding psychopharmacological treatment. Information about psychopharmacological treatment will be registered at both baseline and endpoint in order to document any changes.

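### HAM-D6 is scheduled about eight times after baseline in every patient, but outside the currently depressed class it serves only as a threshold, and no baseline-adjusted longitudinal comparison of the score is listed

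*Protocol article*

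**What the plan says.** The Design section states the aim as the effect of family psychoeducation "on the course of the illness in patients with a diagnosis of major depression", with no severity limit. The Abstract plans "A total of 100 patients, each accompanied by one relative".

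Under Assessments, patients are seen at baseline, "within 2 weeks after the relatives have attend the fourth and last group session", and at 9 months. The text after Table 1 adds that "telephone calls will be made to patients every 6 weeks in the follow-up period" to obtain "information on the presence of depressive symptoms measured by the HAM-D_6". No class of patient is exempt from the calls.

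The Outcomes section uses these ratings in three ways:

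- Remitted patients: relapse at a score of 7 or more (primary outcome). Time to relapse is secondary.
- Partially remitted patients: time to a score below 5.
- Hypothesis 3: "and the reduction of depressive symptoms in the HAM-D_6_-score (hypothesis 3". The Aim limits this to one class: the intervention "will reduce depressive symptoms (measured on the HAM-D_6_) among currently depressed patients".

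Depressive symptoms on the MDI appear among the exploratory comparisons, with no subgroup limit. Statistical analyses names the Mann-Whitney test, Kaplan-Meier and Cox methods, and last observation carried forward for missing data. It names no method for the HAM-D6 score.

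**The concern.** The trial asks about the course of illness and pays for a repeated severity rating in everyone. The listed outcomes then compare that rating as a score only in the class for which 15 to 20 patients per arm at most are planned, as a reduction with no stated time point. In the other two classes, change that does not cross a cut-off leaves no trace in any listed HAM-D6 outcome.

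Two things are at stake. Hypothesis 3 may be able to detect only a very large effect when the ratings already scheduled could do better. And no listed HAM-D6 outcome describes severity over time in all randomized patients. Adding one after the data are in would look post hoc.

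**Working it through.** The plan gives no figure to reproduce here: its only sample size calculation is for relapse, and it says none can be done for hypotheses 2 and 3. It gives no HAM-D6 standard deviation, correlation or expected effect, so those below are assumptions.

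**Number of ratings.** Design says "The second phase is a follow-up conducted 9 months after completion of treatment". Nine months is 9 × 365.25 / 12 / 7 = 39.1 weeks, so calls fall at weeks 6, 12, 18, 24, 30 and 36. Six calls + one post-intervention + one 9-month rating = 8. This assumes HAM-D6 is rated at both visits, because the content of Table 1 is not shown. Over 100 patients that is 800 ratings.

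**Size of the currently depressed class.** Sample size calculation plans 30 per arm for hypothesis 1 and 15–20 per arm for hypotheses 2 and 3. The total of 100 fits 2 × 30 + 2 × 20, so hypotheses 2 and 3 appear to share 30–40 patients. Counted separately the total would be 120–140. The currently depressed class is therefore at most about 15–20 per arm. An even split of 40 patients between the two hypotheses would leave 10 per arm.

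**Ratings outside the only HAM-D6 severity comparison.** With 40 currently depressed patients, 60 × 8 = 480 of 800 (60%). With 30, 70 × 8 = 560 (70%). With 20, 80 × 8 = 640 (80%).

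**Detectable difference.** Two-sample t test, two-sided 5%, 80% power, in SD units of one rating. The base value is 1.32 at 10 per arm, 1.06 at 15, 0.91 at 20 and 0.57 at 50. Multiply by the factor for the analysis, with the same correlation ρ between all pairs of ratings:

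- single raw change: √(2(1 − ρ)); at ρ = 0.5, √1 = 1.00
- single baseline-adjusted score: √(1 − ρ²); at ρ = 0.5, √0.75 = 0.866
- baseline-adjusted mean of seven ratings (six calls and 9 months): √((1 + 6ρ)/7 − ρ²); at ρ = 0.5, √(0.571 − 0.25) = 0.567

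| Per arm | Raw change | Single adjusted score | Adjusted mean of seven |
|---|---|---|---|
| 10 | 1.32 | 1.15 | 0.75 |
| 15 | 1.06 | 0.92 | 0.60 |
| 20 | 0.91 | 0.79 | 0.52 |
| 50 (all patients) | 0.57 | 0.49 | 0.32 |

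Range at 15 per arm for ρ = 0.3 and 0.7: raw 1.25 and 0.82; single adjusted 1.01 and 0.76; mean of seven 0.59 and 0.53. At 20 per arm: 1.08 and 0.70; 0.87 and 0.65; 0.51 and 0.46. Adding the post-intervention rating (eight in all) gives 0.59 at 15 and 0.51 at 20 when ρ = 0.5.

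**Average against 9 months.** The gain in the last column belongs to the follow-up average. The average is the more sensitive target only if the mean effect over follow-up exceeds 0.567 / 0.866 = 0.65 of the 9-month effect.

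**The case against.** The plan sets three class-specific hypotheses and matches an outcome to each. Clinical events are a legitimate choice for remitted and partially remitted patients, and course of illness can be read as the umbrella over relapse, remission and symptom reduction. How a secondary score is modelled is commonly left to the analysis plan, which is not shown. This largely stands: the plan contains no error of arithmetic or contradiction here. What remains is that the article enumerates its outcomes and their populations, and a longitudinal HAM-D6 comparison is not among them.

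A reader might infer more than the document supports:

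- *That most of the ratings are never used.* The six-weekly ratings help to detect and date relapse and remission. The loss comes from reducing them to thresholds.
- *That severity is compared only in the depressed class.* That holds for HAM-D6. The MDI comparison carries no subgroup limit, though it is exploratory and the calls are described as collecting HAM-D6.
- *That hypothesis 3 rests on one unadjusted rating.* The text says only a reduction and names no method. Raw change is one reading.
- *That worsening in a partially remitted patient is bound to be missed.* Time to relapse and the count of recurrences state no explicit class limit.
- *That the gain is from about 1.3 to 0.3 SD.* That contrast mixes sample size, baseline adjustment and number of ratings. It also assumes the same standardized effect in all classes, for which the document gives no support.

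The section on differences between the groups also expects the effect to develop over time. An average over follow-up would dilute such an effect, which is why the 9-month contrast belongs beside it.

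**Conclusion.** The point holds as a missed gain in precision. The safest measure of its size is within the currently depressed class, where no common effect across classes need be assumed. At ρ = 0.5 the detectable difference falls from 1.06 to 0.60 SD (15 per arm) or 0.91 to 0.52 SD (20 per arm) if the alternative is a single raw change. If the alternative is a single baseline-adjusted score, the starting points are 0.92 and 0.79 SD.

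These figures assume equal correlations, no attrition and no clustering by treatment group. A 9-month contrast alone would stay near the single-score values. The all-patient figure of about 0.3 SD (0.28–0.32 for ρ from 0.3 to 0.7) is optimistic: it also ignores the HAM-D6 floor in remitted patients and differing effects between classes. It should not be used as a power claim.

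**What to change.** In Secondary outcomes and Statistical analyses:

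1. Analyse hypothesis 3 with a repeated-measures mixed model of all scheduled post-baseline HAM-D6 ratings, adjusted for baseline HAM-D6, in place of a reduction with last observation carried forward.
2. Fit it in all randomized patients, with arm, time, arm-by-time, baseline depression class and arm-by-class terms. Fix one definition of class for this purpose, since the Aim gives cut-offs on HAM-D6 and Participants gives them on HAM-D17.
3. Take as the hypothesis 3 estimate the arm difference averaged over follow-up in the currently depressed class, and show the 9-month contrast with it.
4. Report the pooled arm difference as a supportive secondary result, always with the class-specific estimates.

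The cost is wording and one model. It needs no new data and does not change the primary outcome. The downside is that the pooled estimate averages over three severity classes and cannot be read alone.

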### Statistics

#### Sample size calculation

Regarding the testing of hypothesis 1, only one similar study in the literature exists that tests an invention similar to the one applied in our study. Shimazu et al. [19] here found a relapse rate in the 9-month follow-up period of 8 % in the intervention group and 50 % in the control group. Based on these findings, 21 patients should be included in each group when using a power of 80 % and type-I error probability associated with the test of the null hypothesis of 5 %. However, we wish to make a more conservative estimate since we acknowledge that our active social support group may also have a positive impact on the outcome results. We therefore plan to include 30 patients in each group to the test hypothesis 1.

Regarding the testing of hypotheses 2 and 3, there are to the best of our knowledge no studies describing this type of intervention to this specific patient group. Therefore, a sample size calculation cannot be performed. Consequently the testing of hypotheses 2 and 3 is more exploratory and we plan to include 15–20 patients in each group to examine both these hypotheses.

#### Statistical analyses

For the statistical analysis SAS software ® will be used.

Baseline characteristics of the invention group and the control group, respectively, will be compared using a *χ*^2^-test regarding categorical variables and an independent samples *t* test regarding numerical variables. The comparison of baseline characteristics will be performed for the whole group of patients independent of subgroup affiliation based on depression levels at baseline.

The number of recurrences in the two groups will be compared using the Mann-Whitney *U* test.

Time to relapse as well as time to full remission (for patients only partially remitted at baseline) will be analyzed using the Kaplan-Meier survival analysis.

To analyze whether the degree of EE in relatives at baseline will be associated with poorer outcome, Cox proportional hazard regression analysis will be applied.

Intention-to-treat analyses will be carried out, meaning that analyses will include all subjects who are randomized.

Regarding missing data the method of Last Observation Carried Forward (LOCF) will be applied.

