## Background

Depression is a frequently occurring disease with an estimated prevalence in Denmark of 3–4 % [1] consistent with findings in other Western European countries [2].

The risk of relapse and recurrence is high [3]. Patients having experienced their first depressive episode have a more than 50 % risk of suffering from a new episode [4]. Furthermore, the risk of subsequent recurrence increases with the number of previous depressive episodes [5].

A robust relationship has been established between family factors and the course of depression, including the risk of relapse [6]. More specifically, relapse has been found to be predicted by the level of expressed emotion (EE) in key relatives defined as a critical, hostile or emotionally over-involved attitude or behavior toward the patient [7]. Several studies have confirmed that patients living with high-EE relatives have a significantly higher risk of relapse than patients living with low-EE relatives [8–11].

Conversely, depression affects the function of the family, as well as impacting on the life of the relatives. Viewing the family as whole, families of patients suffering from depression are characterized by reduced family functioning compared to both nonclinical families and families of patients with schizophrenia or bipolar disorder [12]. Furthermore, relatives of depressed patients report significantly lower levels of quality of life in terms of “psychological wellbeing” compared to the general population [13].

Depression not only causes distress for the patient but also for their close relatives. Relatives of patients with depression report significantly more difficulties than nonclinical families and these difficulties seem to persist even when there is symptomatic remission [14].

Thus, there is a clear link between family functioning and the course of depression. It has previously been suggested that family intervention would be a meaningful and important supplement to psychotherapy and psychopharmacological treatment [15]. These family-oriented practices include a spectrum of therapeutic interventions, covered by the term family therapy and also include family psychoeducation (FPE) [16]. Family psychoeducation is already an evidence-based practice in the treatment of both schizophrenia and bipolar disorder [17].

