### Randomization

After baseline assessments the relatives are randomly assigned (1:1) to either the psychoeducation group or the social support group. The randomization design is a blocked design with 10 relatives in each block. In order to ensure a balanced distribution of both “treatments” in each of the two blocks, a computerized randomization procedure (Microsoft Excel©) will be used to generate randomization codes. The codes will be placed in envelopes. The randomization performed each time a relative is included in the study is performed by a secretary affiliated to the Research Unit at Mental Health Centre North Zealand but not otherwise involved in the study.

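### Baseline is significance-tested in the pooled sample, which is no hypothesis's population, and the named arm comparisons make no use of baseline severity

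*Protocol article*

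**What the plan says.** Under Statistical analyses, the Protocol article compares baseline characteristics between arms with chi-square tests for categorical variables and t tests for numerical ones. It then states: "The comparison of baseline characteristics will be performed for the whole group of patients independent of subgroup affiliation based on depression levels at baseline".

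None of the three hypotheses is tested in that population. Primary outcome restricts relapse to remitted patients. The Aim section assigns hypothesis 2 to partially remitted patients and hypothesis 3 to currently depressed patients. The Sample size calculation plans 30 per group for hypothesis 1 and 15 to 20 per group for hypotheses 2 and 3.

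Allocation is 1:1, and "The randomization design is a blocked design with 10 relatives in each block". No stratification factor is named.

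The arm comparisons named are Mann-Whitney U for the number of recurrences and Kaplan-Meier for the two time-to-event outcomes. Cox regression appears once, to relate expressed emotion at baseline to outcome. For hypothesis 3 the Secondary outcomes section gives only an outcome label, "the reduction of depressive symptoms in the HAM-D_6_-score (hypothesis 3"), and no method is attached to it.

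Baseline prognostic information is at hand. HAM-D6 is in the key to the assessment table and defines the populations in the Aim section. Illness history is recorded at baseline, and the Background says that "the risk of subsequent recurrence increases with the number of previous depressive episodes".

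**The concern.** Two stated choices work against each other. The only baseline check described looks at everyone randomized, while the primary result is read in a pre-defined part of the sample whose balance nothing in the allocation scheme secures. Significance tests do not help: under randomization their null hypothesis is known to be true, and a non-significant result neither shows balance nor removes imbalance.

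The named treatment comparisons, meanwhile, cannot absorb a chance imbalance, because they take no covariates. Relapse is defined by crossing a HAM-D6 threshold, so the baseline score on that scale is an obvious candidate prognostic factor. With about 30 per arm, a reassuring pooled baseline table could sit beside a visible imbalance in the patients who carry the primary result, with no prespecified adjusted analysis among the named methods to settle the question.

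**Working it through.** **The plan's own figure.** Inputs from the Sample size calculation: the earlier trial "found a relapse rate in the 9-month follow-up period of 8" per cent "in the intervention group and 50" per cent in the control group, from which "21 patients should be included in each group when using a power of 80" per cent and a "type-I error probability associated with the test of the null hypothesis of 5" per cent. Sidedness is not stated; two-sided is assumed. The normal approximation is n = [z(0.975)√(2p̄q̄) + z(0.80)√(p₁q₁ + p₂q₂)]² / (p₁ − p₂)², with p̄ = (0.50 + 0.08)/2 = 0.29.

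- Without continuity correction: 18 per group. With it: 22.
- Fisher exact power: 80.6% at 20 per group and 82.5% at 21.

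The stated 21 is therefore reproduced to within one patient. At the planned 30 per group, power for 50% against 8% is 96.7% (94.9% by Fisher's test). On the article's own planning rates, hypothesis 1 has no power shortfall.

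**Chance imbalance by population.** With n per arm, a standardized baseline difference has SD √(2/n) and 95% range ±1.96√(2/n).

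| Population | n per arm | 95% range |
|---|---|---|
| Whole group | 50 | ±0.39 |
| Hypothesis 1 | 30 | ±0.51 |
| Hypotheses 2 and 3, upper plan | 20 | ±0.62 |
| Hypotheses 2 and 3, lower plan | 15 | ±0.72 |

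The last two rows read 15 to 20 per group as applying to each hypothesis. If it covers both together, as the total of 100 suggests (2×30 + 2×20 = 100), each range is wider still.

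**What the pooled test reveals about the subset.** The pooled difference is (30·d₃₀ + 20·d₂₀)/50, with independent normal d₃₀ and d₂₀ (400,000 simulated trials, equal splits assumed).

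- If the 30-per-arm subset differs at p<0.05, the pooled test is non-significant in 59% of cases.
- A standardized difference beyond 0.4 in the subset has probability 12.0%, and still 9.3% when the pooled test is non-significant.

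**Events available for adjustment in hypothesis 1.** 30×0.50 + 30×0.08 = 15 + 2.4 = 17.4 expected relapses. With treatment and one covariate that is 17.4/2 = 8.7 events per coefficient, which leaves no room for a second covariate.

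**Hypothesis 3, if an unadjusted change score were used.** Let r be the baseline to follow-up correlation (not given; 0.3 to 0.7 assumed) and k the ratio of baseline SD to follow-up SD. In units of the follow-up variance, change has variance 1 + k² − 2rk and the baseline-adjusted score has 1 − r². The ratio adjusted/change is (1 − r²)/(1 + k² − 2rk), which reduces to (1 + r)/2 at k = 1.

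| r | ratio, k = 1 | ratio, k = 0.5 |
|---|---|---|
| 0.3 | 0.65 | 0.91/0.95 = 0.96 |
| 0.5 | 0.75 | 0.75/0.75 = 1.00 |
| 0.7 | 0.85 | 0.51/0.55 = 0.93 |

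At k = 1, r = 0.5 and 15 per arm, the difference detectable with 80% power is 1.02 SD for change and 0.89 SD with adjustment. The k = 0.5 column is relevant because these patients enter above a floor of 13 (given on HAM-D6 in the Aim section and on HAM-D17 under Participants), which can compress baseline variance.

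**The case against.** The strongest reply is that covariate lists usually sit in an analysis plan or full protocol, neither of which is shown, and that the article never says baseline tests replace adjustment or steer the analysis. That is right as far as it goes, and the mere absence of a covariate list is no fault. What remains is what the article does fix: the tests, their pooled population, and arm comparisons by methods that take no covariates.

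Four stronger readings are tempting, and the document does not support them.

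- *The primary comparison is unprotected or biased.* The subset is defined by a score taken before randomization, so the comparison within it stays randomized, and chance imbalance is covered by the test's error rate.
- *Hypothesis 3 is analysed as a raw change score.* The article gives a label, not a method. A reduction analysed with baseline as covariate yields the same treatment estimate as an adjusted follow-up score.
- *Change is always less precise by a known amount.* The (1 + r)/2 ratio needs equal SDs; at r = k the change score loses nothing.
- *Remitted patients start just below the threshold of 7.* The entry definition allows any lower score, and no baseline distribution is given.

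A further objection stands in part: with about 17 relapses, 2.4 of them expected in the intervention arm, an adjusted relapse model can be unstable, and the precision gain for a continuous outcome does not carry over to an odds ratio. That limits the adjustment to one covariate; it does not argue against it.

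**Conclusion.** The point holds as a worthwhile improvement to stated methods, not as a flaw that invalidates any comparison. Baseline testing is aimed at a population in which no hypothesis is tested, and it would miss about 59% of the imbalances that reach p<0.05 in the primary subset. This figure assumes 30 of 50 per arm are remitted and a normally distributed covariate. Baseline severity, already available, goes unused in the named arm comparisons.

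The document allows no estimate of the gain for the relapse outcome. For hypothesis 3, which the article itself calls more exploratory, adjustment reduces variance by 15% to 35% relative to an unadjusted change score if SDs are equal and r lies between 0.3 and 0.7. The reduction is only 0% to 7% if the baseline SD is half the follow-up SD. It arises only if an unadjusted change score would otherwise be used.

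**What to change.** 1. Remove the baseline significance tests. Tabulate baseline by arm within each of the three hypothesis populations, with the pooled table as an addition if wanted.
2. Prespecify baseline HAM-D6 as the single covariate in a Cox model for time to relapse and for time to full remission, keeping Kaplan-Meier curves for display, and in the relapse comparison for hypothesis 1. Add no further covariates there, given about 17 expected events, and name a penalized fit in case the model does not converge.
3. State that hypothesis 3 and the continuous exploratory scales are analysed as follow-up score adjusted for baseline.

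The cost is analysis wording and slightly more modelling; no new data are needed. Recruitment was still open when the article was written, so the wording could be settled before outcomes were complete. The drawback is that the adjusted relapse and time-to-event models estimate a conditional rather than a marginal effect, which the report should say.
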